## Methods/Design

In a three-armed block randomized controlled trial (RCT), 27 large cities has been stratified within three regions in the Netherlands (North-East, West, South) and each city has been assigned to one of two intervention groups or the control group using nQuery Advisor® Version 7.0. As a result of the inspection procedure of the Dutch labor inspectorate, i.e. unannounced work site inspections in a well-defined area and time period in the Netherlands, the interventions take place at construction companies working in larger cities.

For the description of the design of the safety intervention and the two guidance strategies, we follow the CONSORT statement [13].

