#### Face-to-face guidance strategy

The face-to-face guidance strategy consists of personal advice at construction companies with a maximum of three visits in which workers are informed about preventing falling hazards with rolling scaffolds, ladders and stairs. The employer or contact person of each construction company is encouraged to involve all their workers in the selection, use and monitoring of safety measures to reduce falling hazards when working with rolling scaffolds, ladders and stairs.

Company visits will take place at the company or at work sites on dates and times agreed on with the contact person of each company during a three-month period. The number of company visits will depend on the size of the company; one visit when <5 workers, two visits when 5–15 workers, and three visits when > 15 workers. It is advisable to contact management and the workers’ council when planning company visits.

Each visit consists of a one- to two-hour interactive consultancy meeting with the contact person and workers of the construction company. Information is exchanged concerning selection, implementation and monitoring of safety measures with regard to rolling scaffolds, ladders and stairs. The safety consultant writes a short report of the findings and the advised safety measures. A maximum of five types of advice can be given, and advice can be added in subsequent visits to the same company. In a company report, advice is grouped into i) the choice and suitability of the equipment for working from heights (i.e. rolling scaffolds, ladders and stairs), ii) safety measures for risk control when using equipment for working from heights, iii) teaching and training, iv) supervising on the selection and safety use of equipment for working from heights, v) remaining advice for improving safe and healthy workplaces.

In total, six safety consultants, experienced in equipment for working from heights, are involved in the face-to-face strategy. In a meeting, these consultants are informed about documented safety measures in the inspection module of the labor inspectorate, safety protocols of employers’ organization providing equipment for working from heights, and two guidelines of Arbouw concerning safe use of rolling scaffolds, and ladders and stairs.

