Dose received refers to the proportion of activities in the intervention that are actually performed by the employer and workers of the construction companies. For both intervention strategies, dose received is assessed by three questions to the employer and two questions to the workers in a questionnaire after completion of the intervention period. For the face-to-face strategy, employers are asked if they have received a safety consultant (yes/no), have given feedback of advice to all workers (yes/no) and have taken preventive actions (yes/no; type of actions: education, training, buying safer equipment, supervision, appointment with suppliers, appointment with principal, other). The workers are asked if they have received information (yes/no) and if they have taken preventive actions (yes/no; type of actions: education, training, following equipment instruction, supervision with colleagues, appointment with suppliers, appointment with principal, other). For the direct mailing strategy, the employers are asked if they have read the postal and internet information (yes/no), if they have disseminated information to all workers (yes/no) and if they have undertaken preventive actions (yes/no; type of actions: education, training, buying safer equipment, supervision, appointment with suppliers, appointment with principal, other). The workers are asked if they have received information (yes/no) and if they have taken preventive actions (yes/no; type of actions: informing, training, following equipment instruction, supervision with colleagues, appointment with suppliers, appointment with principal, other).

Satisfaction is measured by asking the employers and workers how they rated their satisfaction with the intervention as a whole and its individual components, on a scale from 0 (not satisfied) to 10 (very satisfied).

Increased knowledge about working safely with rolling scaffolds, ladders and stairs as a result of the intervention is measured by asking the employers and workers to what extent their knowledge increased from (0–10; 0 = not more knowledge, 10 = much more knowledge). The rates are defined as not more knowledge (0), little (≥0 and <6), moderate (≥6 and <7.5) or much more knowledge (≥7.5).

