Effect on working safely with rolling scaffolds, ladders and stairs as a result of the intervention is measured by asking the employers and workers to what extent the perceived effect on safety behavior is rated (0–10, 0 = no effect, 10 = large effect). The rates are defined as poor (<6), moderate (≥6 and <7.5) or good (≥7.5).

The process outcomes will be measured after the intervention period through questionnaires sent to the companies and their workers.

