### Statistical analyses

The primary outcome measures, i.e. ascertained safety violations, will be presented for the two guidance strategies and the control condition using descriptive statistics. The number of safety violations concerning the installing and use of equipment for working from heights at worksites of painting and maintenance companies ascertained by the Dutch labor inspectorate in the included 27 cities during three weeks in May 2014 will be retrieved by the primary researcher (HM) from the database of the Dutch labor inspectorate. Differences in the mean number of safety violations will be tested using an analysis of variance.

The three process measurements (i.e. satisfaction, insight and safe working behavior) of both intervention strategies are post-tested and converted into continuous variables on a scale of 0–100. The differences between both interventions are examined using independent t-tests.

The analysis is performed on an intention-to-treat basis. IBM SPSS 19.0 will be used for the statistical tests. Statistical significance is defined as p < 0.05 for all outcome measures.

The costs calculation for each intervention strategy will be analyzed descriptively.

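### The independent t-tests on the process scores ignore clustering by company and randomised city, so applied to individual answers their type I error exceeds 5% by an amount the article does not allow one to fix

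*Protocol article*

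**What the plan says.** The protocol article, Statistical analyses, states that the three process scores "are post-tested and converted into continuous variables on a scale of" 0–100, and then: "The differences between both interventions are examined using independent t-tests". The threshold follows: "Statistical significance is defined as p < 0.05 for all outcome measures". No company or city term, cluster-level summary or adjusted standard error is named.

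The Process evaluation section describes who answers: "The process outcomes will be measured after the intervention period through questionnaires sent to the companies and their workers". Each score is asked of both roles, for example: "Satisfaction is measured by asking the employers and workers how they rated their satisfaction with the intervention as a whole". Knowledge and perceived effect are likewise asked of employers and workers.

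The structure above the respondent is also given. Guidance is delivered to companies (Setting). The face-to-face section foresees companies of quite different size: "one visit when <5 workers, two visits when 5–15 workers, and three visits when > 15 workers". Allocation is by city: "each city has been assigned to one of two intervention groups or the control group", with nine cities per arm.

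**The concern.** An independent t-test treats every observation in an arm as unrelated to every other. The design gives two reasons why individual answers are not. Workers of one company share the same visits or mailing and depend on the same employer to pass the content on; the dose-received questions ask employers exactly whether they did so. Companies in turn belong to cities, and the city is what was randomised.

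If answers within a company or city resemble each other, the t-test's standard error is too small. A company with more respondents also counts for more, although nothing in the article says the comparison is meant to be weighted by company size.

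These tests are the only planned comparison of the strategies on acceptability. The Methodological considerations warn that the primary comparison may lack power, so a nominally significant acceptability result could carry weight in choosing which strategy to implement.

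**Working it through.** **Inputs from the article.** Independent t-tests at p < 0.05 (sidedness not stated for these tests; two-sided assumed); city allocation, nine per arm; delivery to companies; size classes below 5, 5–15 and above 15 workers.

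**Not in the article.** SD, ICC, number of companies and respondents per company for the process scores. There is therefore no figure to reproduce on this point. The stated 64 locations per group belongs to the primary outcome. It reproduces as a three-group chi-square test with 2 df on 84%, 69% and 59% (power 0.806 at 64) and has no bearing here.

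**Step 1: closed form, equal company sizes.** With m respondents per company and within-company ICC ρ, the true variance of an arm mean is DE = 1 + (m − 1)ρ times what the t-test assumes. With no strategy effect it rejects with probability 2[1 − Φ(1.96/√DE)]. Example: m = 10, ρ = 0.10 gives DE = 1 + 9 × 0.10 = 1.9, 1.96/√1.9 = 1.42, and rejection in 15.5%.

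| m | ρ 0.01 | 0.05 | 0.10 | 0.20 | 0.30 |
|---|---|---|---|---|---|
| 2 | 5.1% | 5.6% | 6.2% | 7.4% | 8.6% |
| 5 | 5.5% | 7.4% | 9.8% | 14.4% | 18.6% |
| 10 | 6.0% | 10.4% | 15.5% | 24.1% | 30.8% |
| 15 | 6.6% | 13.3% | 20.6% | 31.5% | 39.0% |

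**Step 2: simulation, unequal sizes.** Assumed: 30 companies in nine cities per arm, one employer plus the workers shown, no strategy effect, 4,000 runs (Monte Carlo standard error near 5%: √(0.05 × 0.95/4000) = 0.34 points). The last three columns give the rejection rate by unit of the t-test.

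| Workers per company | Company ICC | City ICC | Respondents | Company means | City means |
|---|---|---|---|---|---|
| 1 or 2 | 0.05 | 0 | 6.0% | 5.4% | 4.7% |
| 1 or 2 | 0.30 | 0 | 10.8% | 4.9% | 4.9% |
| 1 or 2 | 0.10 | 0.05 | 12.6% | 9.3% | 4.3% |
| 2, 5 or 10 | 0.10 | 0 | 12.2% | 4.9% | 5.1% |
| 2, 5 or 10 | 0.10 | 0.05 | 23.8% | 10.2% | 5.0% |
| 3, 10 or 20 | 0.10 | 0 | 19.0% | 4.5% | 4.2% |
| 3, 10 or 20 | 0.30 | 0 | 37.1% | 5.2% | 5.0% |
| 3, 10 or 20 | 0.10 | 0.05 | 36.1% | 12.2% | 4.9% |

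Company means restore 5% only when cities do not differ. City means hold it throughout. The simulated city summary was the plain mean of a city's respondents. A mean of company means keeps the city as the independent unit, so the same reasoning covers it, although it was not simulated. Clustering by the six consultants, who serve the face-to-face arm only, was not modelled.

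**Step 3: weight.** If everyone answers, a company with 20 workers and an employer supplies 21 observations and one with 3 workers supplies 4, so the larger counts 21/4 = 5.25 times as much.

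**Step 4: role mix, only if employers and workers are pooled.** Bias = (employer–worker gap) × (difference in employer share between arms). Assumed gaps of 0.2–0.5 SD and share differences of 10–20 points give 0.02–0.10 SD. With 100 respondents per arm the standard error is √(2/100) = 0.141 SD, and rejection is 5.2% to 10.9%. Equal shares give no bias.

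**The case against.** The article never states the unit of the t-test. A t-test on city means is also an independent t-test, and a condensed article may leave respondent-level handling to the full plan. This limits the point to tests on individual answers. It does not remove it, because the article does name the test, describes rescaling of the scores directly before it, and mentions no aggregation.

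Three stronger readings are tempting, and the documents do not support them.

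- **Employers and workers form one sample.** A reader might infer this from three measurements and a single sentence on testing. The text says neither that the roles are pooled nor that they are kept apart, and the dose-received questions already distinguish them. With separate tests, company clustering remains for workers. An employer-only test with one employer per company would leave city and consultant clustering.
- **The role mix drives the result.** This needs pooling, a gap between roles and unequal shares, none of which is stated. A 1-point gap with SD 1.5 (0.67 SD), 150 respondents per arm and employer shares of 20% against 40% would give 21% rejections, and 30% against 60% would give 41%. But at one employer per company, a 60% share means 1/0.6 = 1.7 respondents per company, where DE at ICC 0.10 is only 1 + 0.67 × 0.10 = 1.07. Settings that make the mix effect large make the clustering effect small, so the two should not be added up.
- **False positives run far above 5%.** That is one end of a range. With one or two responding workers per company and no city effect, the error is 6.0–10.8% for ICC 0.05–0.30.

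It is also fair that these are process measures and not the primary outcome.

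**Conclusion.** The point holds in limited form. A t-test on individual answers assumes an independence that the nesting in companies and randomised cities does not give. Its type I error exceeds 5% for any positive ICC at either level, and companies with more respondents weigh more. The size cannot be derived from the article. Under the assumptions above it runs from about 5–6%, through 10–24% at 10 respondents per company and ICC 0.05–0.20, to over 30% with many respondents and a large ICC or an added city effect. Bias from the employer share is possible only if the roles are pooled. The consequence is confined to the acceptability comparison between the two strategies; the conclusion on safety violations does not depend on it. It should be corrected because the rule is stated and the repair is cheap.

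**What to change.** Rewrite the sentence on the t-tests so that satisfaction, knowledge and perceived effect are analysed separately for employers and for workers, and the strategies are compared in one of two ways:

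- a mixed model with random effects for company and city, region (the randomisation stratum) as a covariate, and small-sample degrees of freedom for nine cities per arm. For employers with one answer per company, the company effect drops out and the city effect stays; or
- a t-test on city-level summaries of company means, which has 9 + 9 − 2 = 16 degrees of freedom if all 18 intervention cities contribute.

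Averaging by company alone is not enough: at an assumed city ICC of 0.05 it still rejected in 9–12% of simulated trials.

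Record company, city and role on each questionnaire. Because recruitment also targets companies with at least 15 workers that are expected to work more widely, the city recorded should be the one through which the company was assigned its strategy.

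The cost is wording and three identifiers. The downside is wider confidence intervals.

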## Discussion

The present randomized controlled intervention study focuses on two frequently advocated strategies to reduce safety violations in the construction industry to gain insight into their effect, implementation and acceptability.

The outcome of this study will help to evaluate the effect of two guidance strategies on reducing safety violations when working from heights with rolling scaffolds, ladders and stairs. When these strategies are effective, stimulation of safety measures through the national institute of safety and health or labor inspectorate can take place to encourage construction companies to comply with safety regulations.

### Methodological considerations

For both guidance strategies, the content and approach has been developed by the Dutch institute on safety and health in the construction industry. Therefore, the practice base has been incorporated to the maximum. For instance, in the face-to-face strategy, the safety consultants have experience in safety in construction work; in the direct mailing strategy, the information materials have been adapted to the context of painters. In addition, construction companies are free to choose how they want to control the safety hazards when working with rolling scaffolds, ladders and stairs. This adds to the number of dynamic implementation strategies which could also be evaluated in actual performance, i.e. reduced number of safety violations. Standardizing the function and process of complex interventions [18] in this study, respectively stimulating the implementation of safety measures [function] and awareness-raising [process], and personal feedback [process] enables the evaluation of such interventions through RCTs. This method of standardization allows the incorporation of two important elements in studying implementation strategies in pragmatic trials [16,19]: 1) tailoring intervention components to context-specific needs of construction companies, and 2) determining the effectiveness of both strategies on different process measures.

Four categories of process measures are proposed in implementation research in the construction industry [20]: awareness of risk factors and control measures; attitude toward changing behavior; ability to change behavior, and actually changing and maintaining behavior. In the present study, three out of four of these aspects are measured: increase in knowledge in safe working with rolling scaffolds, ladders and stairs, attitude in terms of satisfaction and perceived effect of the interventions, and behavior in terms of the primary outcome measure of safety violations.

A constraint of this study is that the ability to effect a behavioral change is not explicitly addressed in the interventions and in the process measures, but it is thought that most of the construction workers are able to comply with the safety regulations when working with rolling scaffolds, ladders and stairs. Another constraint is the measurement of safety violations through the inspection procedure of unannounced work site inspections in a well-defined area and time period in the Netherlands. Therefore, a possible lack of power can emerge due to a lack of the intervention companies when the labor inspectorate is inspecting work sites in 18 of the 27 cities. Due to ethical reasons, i.e. introducing unequal risk of incurring financial penalties when safety violations are established by the labor inspectorate, all construction sites in the 27 cities can be the subject of inspection and the researchers will not reveal the names of the 18 intervention cities nor the names of the participating painting companies.

The results of the present study will be available in the second half of 2014.
